**1. Study Synopsis**

| Protocol Title | Evaluation of the Effectiveness of Chlorhexidine Bathing in Reducing Nosocomial Infections in the Neonatal Intensive Care Unit |
| --- | --- |
| Protocol Number |  |
| Sponsor |  |
| Primary objective | To determine if daily bathing with chlorhexidine impregnated  washcloths will reduce the incidence of bloodstream infections within the neonatal intensive care unit (NICU) . |
| Study design | This is a prospective, controlled; crossover study of daily bathing with no-rinse, 2% CHG impregnated washcloths versus bathing with water/soap or water according to gestational age and weight (e.g. standard bathing). The trial will take place in the NICU.  **In the preliminary phase of the study we will establish the safety of chlorhexidine bathing using Clinell ® Chlorhexidine wash cloths on three groups of patients: term infants admitted to the NICU; late preterm infants (34-37 weeks); preterm infants 30-34 weeks of gestation. Interim analysis for adverse events will be performed after each group of patients.**  **In the subsequent phases of the study,** all infants admitted to the NICU and enrolled in the study will be bathed three times a week with Clinell ® Chlorhexidine wash cloths during the initial 6-months study period (intervention), followed by standard bathing during the second 6-months period, then again intervention period for 6 months and standard bathing for 6-months. Total study period- 2 years.  Data collection will include all bloodstream infections as well as surveillance cultures |
| Number of subjects | Approximately 800 patients in both arms  **Up to 60 patients (at least 200 patient days) in the preliminary study** |
| Study population | Infants **>=10** days ,weighing **>=1500** grams admitted to the NICU |
| Duration of participation | Duration of NICU stay OR for the duration of invasive hardware (e.g intravacular catheters, nasogastric tubes etc. ) |
| Treatment | Bathing three times a week with either:  a.2% chlorhexidine gluconate cloth  b. water/mild soap +water |
| Assessment of efficacy | The primary efficacy endpoint will be the reduction in bloodstream infections incidence during those study periods where the 2% Chlorhexidine Gluconate Cloth will be utilized.  Additional study endpoints include overall incidence of colonization with multi-drug resistant organisms (MDRO) and time to colonization |
| Safety | Safety will be assessed through the monitoring of adverse events  associated with bathing products to include any skin rashes or  hypersensitivity reactions. |

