**5.4 Preliminary study**

**In order to establish safety , we will enroll infants admitted to the NICU to three successive treatment groups , as follows: the first group will include term infants admitted to the NICU (gestational age ≥37+6 and >7 days old), the second group will include near-term infants (gestational age > 34+0 to 36+6 weeks and >7 days old) and the third group will include premature infants (gestational age >30+0 to 33+6 and >=10 days old). We intend to enroll up to 20 patients in each group, for a minimum of 200 patient days per group (see sample size estimation). All infants will be assigned for bathing three times a week with washcloths impregnated with 2% chlorhexidine gluconate (Clinell ® Chlorhexidine wash cloths, GAMA healthcare) for the duration of their NICU stay. The infant’s skin will be monitored continuously as described below (see ‘6.0 Safety and monitoring’ and appendix 2). In case of grade 3 or 4 reactions, the study interventions will be temporarily suspended, and the adverse event will be reported to the Helsinky committee and to the study steering committee. If no grade 3 or 4 reactions will be encountered after at least 200 patient days per group, enrollment to the subsequent group will be performed (e.g if no grade 3-4 reaction will be encountered for 200 patient days in group 1, we will start enrolling patients for group 2 etc.). If no grade 3-4 dermatitis is encountered in the preliminary study, we will initiate enrollment as described below (‘5.5 intervention’)**

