**5.9 Statistical analyses**

Changes in the rates of BSI and clinical sepsis will be compared between the intervention and the control period. Continuous variables will be examined with the use of two-sample t-tests and linear regression modeling, and categorical variables will be examined by means of Fisher’s exact test. Cox proportional-hazards regression model will be used to compare the time from admission until the first primary bloodstream infection , clinical sepsis or acquisition of MDRO between the control and intervention periods.

**Sample size calculation:** based on our ongoing surveillance, there are 2-3 BSI events per 1000 patients –days in our NICU. In order to detect a 50% reduction in BSI rates , we will need 37,096 patient days (18,548 in each group) in order to have 80% power to reject the null hypothesis, with 0.05 level of significance. Currently, our average annual census is 45,000 patient days. therefore, a 2-year study will have >80% power to reject the null hypothesis (the BSI rates in the control period equal the rates in the intervention period).

**For the preliminary study, we used the data in Milstone et al. ^18^ who reported no serious adverse skin reactions and an incidence of 1.2 minor skin reactions per 1000 patient days. A sample of 500 patient days will enable us to detect a ten-fold higher rate of minor skin reactions. Therefore at least 200 patient days in each group of the preliminary study (>600 patient days), would suffice.**

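### About 800 patients, a 37,096 patient-day requirement and a power claim drawn from the whole-unit census are never reconciled, so the stated >80% power has no valid basis

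*Protocol*

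**What the plan says.** The planned size appears in two places, in different units.

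- **Synopsis, Number of subjects:** "Approximately 800 patients in both arms".
- **Section 5.9, Sample size calculation:** the background rate is given as "there are 2-3 BSI events per 1000 patients –days in our NICU". The target effect is a halving of the BSI rate, and "we will need 37,096 patient days (18,548 in each group) in order to have 80% power to reject the null hypothesis", at a significance level of 0.05. Sidedness is not stated. The text continues "Currently, our average annual census is 45,000 patient days" and concludes from this that two years give more than 80% power.

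Other passages limit who contributes days. The synopsis and section 5.5 restrict the main study to infants of at least 1500 g and at least 10 days of age, and section 5.5 adds parental consent. The synopsis lets participation last for the NICU stay or for the time that invasive devices are in place. No mean participating stay is given, and neither is the eligible or consenting share of the census.

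Two passages bear indirectly on days per infant. Section 5.4 says of the preliminary phase: "We intend to enroll up to 20 patients in each group, for a minimum of 200 patient days per group". Section 4 cites US hospital stays for very low birth weight infants of 79 days with sepsis and 60 days without.

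**The concern.** The census sentence is the only support offered for the power of the two-year study, and it counts days that cannot enter the analysis. The synopsis offers a second measure of size, a number of infants, and nothing converts it into patient-days. A reader cannot tell whether the trial is sized by 800 infants, by 37,096 days or by two calendar years. These can imply very different power.

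If eligible exposure falls well below 37,096 days, a non-significant result could be read as evidence against chlorhexidine bathing when the trial had limited ability to detect even a halving of the rate.

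**Working it through.** **Inputs.** From section 5.9: control rate 2 to 3 per 1000 patient-days (2.5 is the midpoint), 50% reduction, 80% power, alpha 0.05, 18,548 days per group, census 45,000 a year. From the synopsis: 800 infants, taken as the total, so 400 per condition. Mean eligible days per infant is **my assumption**, varied from 10 to 60.

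**Formulas.** With rates λ1 and λ2 per day and n patient-days per condition:

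- n = (z_α + z_β)² (λ1 + λ2) / (λ1 − λ2)²
- power = Φ[(λ1 − λ2) √(n / (λ1 + λ2)) − z_α]

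These treat patient-days as independent and ignore clustering by infant and period.

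**1. The plan's own figure.**

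- One-sided 0.05, 2 vs 1 per 1000: 6.1826 × 0.003 / 0.001² = 18,548, an exact match.
- Two-sided 0.05, 2.5 vs 1.25 per 1000: 7.849 × 0.00375 / 0.00125² = 18,837, which is 1.6% above the stated figure (18,801, or 1.4% above, with the pooled two-proportion formula).
- Two-sided at 2 per 1000 gives 23,547 and at 3 per 1000 gives 15,698; neither fits.

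So 37,096 is a sound figure for some stated-range inputs, but which inputs were used cannot be determined. I use two-sided tests below.

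**2. The census against 800 infants.**

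- Two-year census: 2 × 45,000 = 90,000 days.
- 90,000 / 800 = 112.5 days per infant.
- At the longest quoted stay: 800 × 79 = 63,200 days, still short of 90,000.

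If every census day counted, power would be 97%, 99% and 99.7% at 2, 2.5 and 3 per 1000. With 800 infants in total, that exposure is not available.

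**3. The requirement against 800 infants.**

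- 37,096 / 800 = 46.4 eligible days each.
- If 800 is per arm: 37,096 / 1,600 = 23.2 days each.
- For 80% power, two-sided: 2 × 23,547 / 800 = 59 days at 2 per 1000; 2 × 18,837 / 800 = 47 at 2.5; 2 × 15,698 / 800 = 39 at 3.

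**4. Power with 800 infants, by assumed mean eligible stay.** Example at 20 days and 2 per 1000: n = 8,000 per condition, 16 vs 8 expected events, 0.001 × √(8,000 / 0.003) = 1.633, and Φ(1.633 − 1.960) = 37%. At 18,548 days per group the expected events would be 37 vs 19.

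| Mean eligible days | Total days | 2 per 1000 | 2.5 per 1000 | 3 per 1000 |
|---|---|---|---|---|
| 10 | 8,000 | 21% | 25% | 29% |
| 20 | 16,000 | 37% | 45% | 52% |
| 30 | 24,000 | 52% | 61% | 69% |
| 40 | 32,000 | 64% | 73% | 81% |
| 46.4 | 37,096 | 70% | 79% | 86% |
| 60 | 48,000 | 81% | 89% | 93% |

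A one-sided test raises these figures: at 2 per 1000 it gives 31%, 50% and 64% for 10, 20 and 30 days. An exact conditional comparison lowers them: at 20 days and 2 per 1000, two-sided, it gives 30% instead of 37%.

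**The case against.** The strongest reply is that the three numbers measure different things: a requirement, a unit census and an approximate enrolment. That stands. A reader might infer that they contradict each other outright, but all three can be true if 800 infants average about 46 eligible days. What fails is using the full census as the exposure of about 800 infants.

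Second, the census leaves room for ineligible days, since 37,096 / 90,000 is only 41%. This also stands, and it means that running for two years is not itself a defect. But the Protocol never says that at least 41% of census days are eligible and consented. For two-sided 80% power the share needed is 52%, 42% or 35% at 2, 2.5 or 3 per 1000.

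Third, 800 may be a forecast and not a cap, because section 5.5 fixes the study by four six-month periods. It may also mean 800 per arm, in which case 90,000 days would need 56 days each and the comparison with 79 days no longer rules it out. Both readings are open. Under either one, the census still includes infants who cannot contribute, and the link from patients to days is still missing.

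Fourth, the Protocol's own stay figures do not show that 800 infants fall short. The preliminary ratio of 200 / 20 = 10 days combines a maximum number of infants with a minimum number of days, so it is a floor and not an expected stay. The 60 and 79 days exceed 46. However, they are whole stays of very low birth weight infants and include time before eligibility, so they serve only as an upper guide.

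**Conclusion.** The point holds as a failure to reconcile, with an unsupported power statement. Section 5.9 credits the trial with every census day although only consented infants meeting the weight and age criteria count, and 800 infants in total cannot supply 90,000 days. The 37,096 figure itself is not the error.

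The size of the problem depends on a mean eligible stay that the Protocol does not give. With 800 infants in total and a two-sided test, power reaches 80% only at about 59, 47 or 39 eligible days each for control rates of 2, 2.5 or 3 per 1000. At an assumed 20 to 30 days it is 37% to 69% across those rates.

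A reader might go further and conclude that the trial is underpowered, or has less than an even chance of detecting the effect. The document does not support that. Power below one half occurs only at the shorter assumed stays, and at 60 days power exceeds 80% at all three rates.

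**What to change.** In section 5.9, replace the census-based inference with the expected eligible, consented patient-days over the four six-month periods. Calculate this as eligible, consented infants × mean days from eligibility to the end of participation, using the unit's own surveillance data. Make the patient number in the synopsis agree with it, and say whether that number is a total or per arm. Then restate the power for that exposure, giving the control rate and sidedness used.

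The cost is one query of existing unit data and a rewording of two passages. The stated power may become less favourable.

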**5.5 Intervention**

All infants in the NICU eligible for the study will be assigned for bathing three times a week with washcloths impregnated with 2% chlorhexidine gluconate (Clinell ® Chlorhexidine wash cloths, GAMA healthcare) during the initial 6-months study period (intervention), followed by standard bathing during the second 6-months period, then again intervention period for 6 months and standard bathing for 6-months. Total study period- 2 years.

**Inclusion criteria**: infants weighing ≥1500 grams and ≥10 days of age; parents’ informed consent

**Exclusion criteria:** infants weighing <1500 grams or <10 days of age**;** parents’ refusal to sign informed consent.

For standard bathing procedure see appendix 1.

Before the study initiation, as well as at the beginning of each study period, nurses will be instructed on the proper technique for bathing patients. Bathing will be performed according to product brochure, three times a week.

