**5.6 Outcome measures**

A. Number of BSI/CLABSI/clinical sepsis events per 1000 patient days during the intervention periods compared with the control periods.

B. Number of new patients colonized with MRSA, VRE, CRAB or ESBL per total number of patients, monthly range and variance.

C. Number of new patients colonized with MRSA, VRE, CRAB or ESBL per 1000 eligible patient days [ Total patient days – total patient days for patients identified with MDRO]

D. Time to colonization with MDRO during the intervention periods compared with the control periods.

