**5.7 Data collection**

Each patient admitted to the NICU during the study periods and meeting the inclusion criteria, will be recorded and assigned a specific study number. The dates of admission and dates of discharge will be recorded and used to calculate length of stay and to determine the

incidence of nosocomial infections based on microbiological data. Clinical and laboratory data, including the use of invasive device (intravascular devices, mechanical ventilation, feeding tubes) will be collected on standardized forms. The data will be coded under a password protected database and linked only to study patient identifier.

Infections and MDRO acquisitions will be monitored during the study period. Events occurring within 2 days after the transition will be assigned to the previous bathing period.

For infection surveillance, daily review of cultures and new orders for antibiotic therapy will be performed for all study participants. Infectious events will be evaluated by an independent investigator blinded to the intervention period.

Active surveillance testing for MDRO will be performed once every two weeks during the study period. Swabs from the nasopharynx (for MRSA)] and from the rectal area (for ESBL producing organisms, VRE and CRAB) will be obtained by unit staff and processed in the microbiology laboratory of Shaare-Zedek Medical Center.

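### The time at risk for the primary comparison is not fixed: participation has two possible ends, and the clock starts at admission, before an infant can enter the study

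*Protocol*

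**What the plan says.** - Protocol, section 1 (Study Synopsis), duration of participation: "Duration of NICU stay OR for the duration of invasive hardware". The examples of hardware include nasogastric tubes as well as intravascular catheters. No rule says which of the two ends applies to a given infant.
- Section 5.5 admits "infants weighing ≥1500 grams and ≥10 days of age", with parental consent.
- Section 5.6, outcome A: "Number of BSI/CLABSI/clinical sepsis events per 1000 patient days during the intervention periods compared with the control periods". Which patient-days count is not stated. Outcome C, a colonization rate, does have its denominator written out: "Total patient days – total patient days for patients identified with MDRO".
- Section 5.7: the dates of admission and discharge are "used to calculate length of stay and to determine the" incidence of nosocomial infection.
- Section 5.7, on the switches between bathing periods: "Events occurring within 2 days after the transition will be assigned to the previous bathing period". The patient-days of those 2 days are not mentioned.
- Section 5.9: the Cox model measures time from admission to the first event. The sample size is 18,548 patient-days per group (37,096 in total), set against a census of 45,000 patient-days per year.

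**The concern.** A rate per 1000 patient-days has meaning only if numerator and denominator cover the same, stated stretch of time. Here the end of that stretch has two versions. The start, where the protocol gives one, is admission, although the study bath is possible only after entry.

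An infant admitted at birth spends at least 10 days on the Cox clock before qualifying, and longer if still below 1500 g. Read literally, an infection on day 5 would count in the bathing comparison although no study bath could have preceded it. Such time carries the same risk in both arms and pulls the rate ratio towards 1.

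The open end of participation is a separate problem. Stopping at hardware removal would change both the base rate and the number of days. The protocol gives no hardware-day figures, so that effect cannot be sized. Because the bathing periods are known to those running the study, the window should not be left to be chosen once data are in hand.

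**Working it through.** **Inputs.** From section 5.9: control rate 2 to 3 per 1000 patient-days, a 50% reduction, 80% power, significance level 0.05, 18,548 days per group, census 45,000 per year (90,000 over two years). From the synopsis: about 800 infants. From section 5.5: entry from day 10. From section 5.5: four 6-month periods in the order intervention, standard, intervention, standard.

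**Assumptions.** All 800 infants are admitted at birth; each has 10 days before entry (15 as a variant); pre-entry events occur at the control rate; tests are two-sided at 0.05 (the protocol does not give the sidedness).

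**The plan's own figure.** Days per group = (z_α + z_β)² (r₁ + r₂)/(r₁ − r₂)².
- At 2 against 1 per 1000 with one-sided 0.05: (1.645 + 0.842)² × 0.003/0.001² = 18,548, an exact match.
- At 2.5 against 1.25 per 1000 with two-sided 0.05: 18,837, about 1.6% higher.

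Power below is Φ(|r₁ − r₂|/√((r₁ + r₂)/D) − 1.96), with D the days per arm.

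**Unexposed share.** 800 × 10 = 8,000 days.
- Of 37,096 days: 8,000/37,096 = 0.216.
- Of 90,000 days: 8,000/90,000 = 0.089.

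**Apparent rate ratio if those days and their events are counted.** f + (1 − f) × 0.50.
- 0.216 + 0.784 × 0.50 = 0.608.
- 0.089 + 0.911 × 0.50 = 0.544.

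**Power at 2 / 2.5 / 3 per 1000, true rate ratio 0.50.**

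| Scenario | Days per arm | Apparent rate ratio | Power |
|---|---|---|---|
| 37,096 days, all exposed | 18,548 | 0.50 | 70% / 79% / 86% |
| 37,096 days, 8,000 unexposed days and events counted | 18,548 | 0.61 | 47% / 56% / 64% |
| The same, those days and events removed | 14,548 | 0.50 | 60% / 69% / 77% |
| 90,000 days, 8,000 unexposed days and events counted | 45,000 | 0.54 | 94% / 97% / 99% |

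Worked example, second row at 2.5 per 1000: the rate difference is 0.0025 × (1 − 0.608) = 0.00098. Its standard error is √(0.0025 × 1.608/18,548) = 0.000466. The ratio is 2.11, and Φ(2.11 − 1.96) = 0.56.

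With 15 days before entry on the 37,096-day base, the share is 12,000/37,096 = 0.32, the apparent rate ratio is 0.66, and power at 2.5 per 1000 is 43% counted against 63% removed.

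**If pre-entry days are counted but pre-entry events are not.** Both rates are multiplied by 0.784 and the rate ratio stays at 0.50. Reported incidence is too low, but the comparison is hardly touched.

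**The 2-day rule.** Of the three switches, two leave chlorhexidine and one enters it. If events move but days do not, and each window still runs at the previous period's rate, chlorhexidine carries 365 + 4 − 2 = 367 days of events and control 365 − 4 + 2 = 363, each over 365 days. The rate ratio is multiplied by 367/363 = 1.011, so 0.50 reads as 0.506. Moving the days as well restores 0.50.

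**The case against.** The strongest reply is that the protocol never says pre-entry events count. Section 5.7 describes infection surveillance for study participants, and an infant below the age or weight limit is not yet one. If only the days slip in, the rate ratio is safe. This stands, and it makes the dilution conditional. It does not settle the matter, because section 5.9 names admission as the Cox origin and section 5.7 ties incidence to admission and discharge dates.

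A second reply is that a person-time rule is often left to the SAP. That is fair for detail, but here the protocol does state a time origin, and it conflicts with the entry criteria.

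Three stronger readings are tempting and are not supported.
- A reader might infer that section 5.4, with bathing "for the duration of their NICU stay", contradicts the synopsis. It concerns only the uncontrolled preliminary phase and agrees with one of the two synopsis options.
- A reader might infer that section 5.6 leaves the post-switch patient-days in the new period while their events move. It counts "events per 1000 patient days during the intervention periods compared with the control periods" and says nothing about switches. The mismatch is a risk that the wording leaves open.
- A reader might infer that the flaw costs the difference between 79% and 56% power. The 79% assumes that all 37,096 days are exposed, which removing pre-entry time does not bring about; the proper comparison is 56% with 69%. The 37,096 is also the required minimum. On the full census base, power stays above 90%.

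**Conclusion.** The point holds as a badly fixed definition. The end of participation is ambiguous, and the stated time origin includes days on which no study bath was possible.

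The size depends on assumptions that the protocol does not settle: admission at birth, 10 days before entry, pre-entry events counted at the control rate, and the total number of countable days. Eligible days must be fewer than census days, so the 90,000-day case is the favourable end. If events are counted, the apparent rate ratio under these assumptions is 0.54 to 0.61 for a true 0.50, and the bias is towards no effect in both cases. Loss of power matters only if the total is near 37,096 days. If events are not counted, the comparison is nearly unaffected.

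The 2-day rule is a minor matter: about 1% on the rate ratio, against chlorhexidine. Nothing here shows the planned 37,096 days to be miscalculated. The change is worth making because it is cheap and removes a choice that could otherwise be made after the data are seen.

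**What to change.** - Define one window for both events and patient-days in outcome A: from enrolment (age, weight and consent all met) to one stated end, for example NICU discharge or death.
- Split each infant's days at the switches between bathing periods, and apply the 2-day lag to patient-days as well as events.
- In section 5.9, start the Cox clock at enrolment, or keep admission as the time scale with delayed entry at enrolment.
- Reconcile the synopsis wording on NICU stay versus hardware duration. When bathing itself stops is for the sponsor to decide; no rule is proposed here.

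The cost is protocol wording plus the date of enrolment, alongside the admission and discharge dates already recorded. The downside is fewer countable patient-days than an admission-to-discharge count: in the example above, 29,096 instead of 37,096.
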